### Recruitment {15}

A combination of listing and stratified simple random sampling approaches will be applied while selecting study participants. The participants will be recruited within the 24 districts (four districts in each region). In each district, a three-stage sampling design will be applied. In the first stage, two sub-counties will be selected at random considering the urban/rural divide (see Table 7). From the selected sub-counties, up to four parishes will be selected at random. From each selected parish, up to 12 villages will be selected at random and a census/listing of all eligible young fathers as per the inclusion criteria (Table 2, above) will be listed with the help of individuals familiar with the villages (i.e., members of village health teams (VHTs) and village leaders (local council chairpersons or LC1 executives) to generate a sampling frame. A total of 24 villages will be sampled from 4 randomly selected parishes in two randomly selected sub-counties in each district.

**Table 7 Tab7:** REAL Fathers external evaluation selected sample

	**District**	**Sub-county**	**Randomization**
1	Amuria	Akeriau	Intervention
2	Amuria	Morungatuny	Control
3	Bugiri	Bulidha	Intervention
4	Bugiri	Iwemba	Control
5	Buikwe	Nkokonjeru Tc	Intervention
6	Buikwe	Buikwe Tc	Control
7	Dokolo	Okwalongwen	Intervention
8	Dokolo	Agwata	Control
9	Hoima	Kyabigambire	Intervention
10	Hoima	Kigorobya	Control
11	Ibanda	Keihangara	Intervention
12	Ibanda	Ishongororo	Control
13	Iganga	Nawanyingi	Intervention
14	Iganga	Nakalama	Control
15	Isingiro	Kabuyanda	Intervention
16	Isingiro	Kashumba	Control
17	Kamuli	Bulopa	Intervention
18	Kamuli	Kagumba	Control
19	Katakwi	Katakwi	Intervention
20	Katakwi	Toroma	Control
21	Kayunga	Kangulumira	Intervention
22	Kayunga	Kayunga	Control
23	Kikuube	Bugambe	Intervention
24	Kikuube	Kiziranfumbi	Control
25	Kiryandongo	Bweyale Tc	Intervention
26	Kiryandongo	Kiryandongo Tc	Control
27	Kole	Ayer	Intervention
28	Kole	Bala	Control
29	Lira	Aromo	Intervention
30	Lira	Ogur	Control
31	Luwero	Bamunanika	Intervention
32	Luwero	Katikamu	Control
33	Masindi	Miirya	Intervention
34	Masindi	Pakanyi	Control
35	Mayuge	Imanyiro	Intervention
36	Mayuge	Mpungwe	Control
37	Mbarara	Kagongi	Intervention
38	Mbarara	Kashare	Control
39	Nakasongola	Nabisweera	Intervention
40	Nakasongola	Wabinyonyi	Control
41	Oyam	Ngai	Intervention
42	Oyam	Otwal	Control
43	Rubirizi	Katerera	Intervention
44	Rubirizi	Kirugu	Control
45	Serere	Kateta	Intervention
46	Serere	Kyere	Control
47	Soroti	Tubur	Intervention
48	Soroti	Asuret	Control

A total of 3744 young fathers and their spouses (i.e., couple dyads) will be recruited (1872 per study arm) for this study, or 156 young fathers and their spouses per district. Study participants will be recruited solely through household visits. All young fathers and their spouses willing to follow the study protocol will go through an informed consent process. In a first step, fathers who meet the study’s eligibility criteria will be contacted and briefly informed about the study and invited for an interview. If consent is obtained, the young father’s female partner (either his spouse or cohabitating girlfriend) will be informed about the study and invited for an interview either on the same day or at a later scheduled date. If both the young father and the female partner agree to take part in the study, written informed consent will be obtained from both.

If the couple is not available on the initial day of contact, up to two additional attempts (for a maximum of three visits) will be made to contact the couple on varying days of the week. If the couple declines to participate or cannot be located after the third visit, a new young father will be randomly selected from the village listing. We will use randomization without replacement to reach the required sample.

## Assignment of interventions: allocation

### Sequence generation {16a}

The study will be implemented in 24 districts in six geographical regions of Uganda. As noted above, in each district, a simple random sample of two sub-counties will be taken. These sub-counties will be randomly allocated to either the treatment or control condition (1:1 within each district) using the Mersenne Twister algorithm via the RAND function in Microsoft Excel [52]. For subsequent follow-up studies (midline and endline), all enrolled participants will be re-interviewed at midline and endline surveys. (See Table 7 for sample randomization of sub-counties data).

### Concealment mechanism {16b}

Allocation concealment will be ensured, as the allocation outcome will not be revealed to enumerators at any point and will not be revealed to the implementing partners until the sub-county and fathers and mothers within the sub-county have been recruited into the trial and after all baseline measurements have been completed.

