**Methods:**

To assess the REAL Fathers intervention, we use a cluster-randomized controlled trial design within 48 sub-counties randomly sampled from 24 districts in six regions of Uganda. Sub-counties were randomly allocated to treatment or control arms at baseline. Study participants are fathers ages 16–25 years and their cohabitating wives whose eldest child is below the age of 3 years (*n* = 3744 couple dyads). Primary outcomes are the following: (1) reduced intimate partner violence; (2) reduced violent discipline of children; (3) increased father-child engagement and play; (4) improved early childhood development. Secondary outcomes include the following: (1) father’s knowledge of and (2) attitudes towards positive parenting and discipline; (3) father’s use of positive parenting and discipline; (4) father’s use of emotional engagement with child; (5) couple communication and conflict resolution; (6) gender equitable household and caregiving decision-making and behaviors; (7) father engagement in child health-promoting activities; (8) improved knowledge of family planning methods; (9) reduced unmet need for family planning; (10) reduced problem alcohol use; and (11) supportive community norms for father-child engagement and play. Longitudinal survey data will be collected by trained enumerators using KoboCollect in six local languages at three time points: one month before the intervention (baseline); one month after the intervention (endline); and nine months after the intervention (follow-up). Intervention effects on primary and secondary outcomes will be assessed using difference-in-differences (DiD) mixed-effects models that account for the clustered design.

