### Trial design {8}

The impact of the REAL Fathers intervention will be assessed using a cluster-randomized controlled trial (cRCT) wait-list control rollout design [44]. This cRCT employs a superiority framework to test the null hypothesis that there will be similar differences in the primary and secondary outcomes from baseline to endline in both the REAL Fathers intervention group and the waitlisted control group receiving standard care [45]. The survey questionnaire will use validated questions, as piloted in a previous evaluation of the intervention [40], and will be extended to include items from Caregiver Reported Early Development Instruments (CREDI) [46] and socio-demographic items adapted to the local context. The phased rollout of the study will involve three cohorts, each with 1872 father-spouse dyads in the control group and 1,872 father-spouse dyads in the intervention group, for a total of 3744 father-spouse dyads across the three cohorts and study arms. Baseline data collection will occur roughly one month before the start of a cohort, with endline data collection occurring roughly 8 months later (i.e., one month after the 7-month mentoring period of the REAL Fathers intervention ends). Follow-up data collection will occur 8 months after endline data collection. This rollout design is optimal for resource constraint and ethical considerations. The trial is designed to match the speed of implementation, with a random sample of study participants in the intervention group selected from the overall implementation cohorts. Due to personnel and resource constraints in reaching the large number of program beneficiaries, staggered implementation of the intervention—and therefore also the cRCT trial which uses a sub-sample of program beneficiaries—is necessary. Further, from an ethical standpoint, in order to offer those in the control conditions of the study an opportunity to participate in REAL Fathers, several implementation cohorts are necessary, making this wait-list control rollout design the most appropriate for the study context.

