### Participant timeline {13}

This cRCT will roll out in a phased manner in conjunction with the larger implementation project using a subsample of individuals in three of the five implementation groups included as the intervention group in the trial. Sufficient time is planned to allow waitlist controls to transition to intervention groups in subsequent implementation rounds after they participate in the follow-up assessment. As shown in Table 6, for each trial cohort, baseline data collection will occur roughly one month before the start of a cohort, with endline data collection occurring roughly 8 months later (i.e., one month after the REAL Fathers intervention group ends). Follow-up data collection will occur 8 months after endline data collection.

**Table 6 Tab6:** Trial schedule: Enrolment, intervention, and assessments (adapted from SPIRIT 2013 Figure [36])

Date	Trial activity	Intervention activity		Cohort		
		REAL Fathers	Standard care	1	2	3
Nov 2023	Cohort 1 (C1) enrolment: eligibility screen and informed consent	Community engagement and sensitization (Steps 1–3)		1		
Dec 2023	C1 baseline assessment	REAL Fathers materials adaptations (Step 4) & Training of trainers (Step 5)		1		
Dec 2023 (after baseline)	Randomization (allocation to control or intervention)	Selection and training of mentors; selection of fathers (Steps 6–9)	x	1		
Jan–Aug 2024		Individual and group mentoring; community posters (Steps 10–11)	x	1		
Oct–Nov 2024	C1 endline assessment (1 mo. after intervention ends)			1		
Dec 2024–Jan 2025		Pause and Reflect				
Jan–Feb 2025	C2 enrolment: eligibility screen and informed consent	Community engagement and sensitization (Steps 1–3)			2	
Feb–Mar 2025	C2 baseline assessment	REAL Fathers materials adaptations (Step 4) & Training of trainers (Step 5)			2	
Mar 2025 (after baseline)	Randomization (allocation to control or intervention)	Selection and training of mentors; selection of fathers (Steps 6–9)	x		2	
Apr–Nov 2025		Individual and group mentoring; community posters (Steps 10–11)	x		2	
Jul 2025	C1 follow-up assessment			1	2	
Dec 2025	C2 endline assessment (1 mo. after intervention ends)				2	
Jan 2026	C3 enrolment: eligibility screen and informed consent	Community engagement and sensitization (Steps 1–3)				3
Feb 2026	C3 baseline assessment	REAL Fathers materials adaptations (Step 4) & Training of trainers (Step 5)				3

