## Assignment of interventions: Blinding

### Who will be blinded {17a}

Sub-county stakeholders, trial participants, enumerators, and the implementing partners will be blinded to allocation until after recruitment and baseline measures are complete.

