## Trial status

The protocol is version 1.2 of December 10, 2024. The trial was initiated in November 2023 and recruitment is expected to be complete in December 2025. Enrolment is active at the time of submission.

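### If the 48 sub-counties were allocated once, as Table 7 shows, concealment from partners and stakeholders holds for Cohort 1 only; the source of the intervention arm is also stated in two incompatible ways

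*Protocol article*

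**What the plan says.** **Concealment and blinding.** Under Concealment mechanism {16b}, the allocation "will not be revealed to the implementing partners until the sub-county and fathers and mothers within the sub-county have been recruited into the trial" and baseline measurement is finished; enumerators are never told. Under Who will be blinded {17a}, stakeholders in the sub-county, participants, enumerators and "the implementing partners will be blinded to allocation until after recruitment and baseline measures are complete". Implementation {16c} hands the sub-county list to the field implementation team once randomization is done.

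**Allocation.** The abstract describes "48 sub-counties randomly sampled from 24 districts in six regions of Uganda" and reports their allocation in the past tense. Table 7, captioned "REAL Fathers external evaluation selected sample", names all 48 with an arm against each. Trial status states: "The protocol is version 1.2 of December 10, 2024".

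**Timing.** Table 6 has the row "C2 enrolment: eligibility screen and informed consent" at January–February 2025 and the matching Cohort 3 row at January 2026. It also shows a randomization after each cohort's baseline: December 2023, March 2025 and February 2026.

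**Source of participants.** Trial design {8} matches the trial to the rollout, "with a random sample of study participants in the intervention group selected from the overall implementation cohorts". The introduction and Participant timeline {13} likewise describe a subsample of programme fathers. Against this, Recruitment {15} says "Study participants will be recruited solely through household visits". That section and Eligibility criteria {10} describe a listing of villages by the research team, with no difference by arm.

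**The concern.** In a cluster trial that enrols individuals after clusters are allocated, randomization protects against selection only if the people who shape the sample, and those deciding whether to join, do not know the arm. Here the evaluation team lists villages with help from village health team members and local council leaders. Partner staff have also already approached community leaders about the programme. If those people know which sub-counties will receive REAL Fathers, the listing and a couple's willingness to consent can differ by arm.

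The second issue would act more directly. Under Intervention description {11a}, fathers enter the programme by volunteering at sensitization meetings or by being named there, followed by screening by project officers. If the intervention arm were sampled from those fathers and the control arm from a household listing, one arm would hold motivated volunteers and the other a cross-section. Difference-in-differences removes stable differences in level. It does not remove a difference in readiness to change, which would breach the parallel-trends assumption on which the analysis relies.

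**Working it through.** **Does Table 7 cover the whole trial?** Sample size {14} gives 156 couples per district, 78 per arm, with one sub-county per arm in each district.

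- Sub-counties: 24 districts × 2 = 48.
- Dyads: 24 × 156 = 48 × 78 = 3,744, the stated total.
- Per arm: 24 × 78 = 1,872, as stated.

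Table 7's 48 rows therefore account for the full sample, and the abstract gives 48 as the trial's number of clusters. Trial design {8} also says that each cohort has 1,872 dyads per arm, which would make 3 × 3,744 = 11,232 in all and contradicts its own total of 3,744. On that literal reading 48 × 78 fits a single cohort. The clusters available to later cohorts would still be the same 48.

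**Is the allocation fixed before later cohorts enrol?** From 10 December 2024 to 1 January 2025 is 22 days; to 1 January 2026 it is 387 days. The protocol does not say how cohorts map to sub-counties, so take both layouts:

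- *Each sub-county belongs to one cohort.* The arms of the Cohort 2 and 3 sub-counties are tabulated before those cohorts enrol, and {16c} releases the list after randomization.
- *Each sub-county hosts several cohorts.* Partners have been delivering in the intervention sub-counties since January 2024, when Cohort 1 mentoring begins, so the arm is visible locally.

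Under either layout, partners and stakeholders cannot be presumed unaware in Cohorts 2 and 3. The March 2025 and February 2026 randomization rows would rescue the claim only if they were new allocations, in which case Table 7 and the abstract are wrong.

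**How much of the trial?** Assuming equal cohorts, 3,744 ÷ 3 = 1,248 dyads each, so Cohorts 2 and 3 hold 2 × 1,248 = 2,496 dyads (66.7%), or 1,248 per arm. The literal per-cohort reading gives 7,488 of 11,232, the same share.

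**Source of the arms, side by side.**

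| Section | Source of participants |
|---|---|
| Introduction; {8}; {13} | Intervention arm is a subsample of programme fathers |
| {11a} | Programme fathers volunteer or are named at meetings |
| {10}; {15} | Everyone comes from the research team's listing and household visits |

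The first and third rows cannot both describe the intervention arm. Table 6 leans towards the third, since it puts programme selection of fathers after baseline. It also runs the sensitization meetings in the same period as trial enrolment, so it does not settle the matter.

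**The case against.** **Tabulated is not the same as known.** The evaluation team holds the randomization, enumerators are never told, and participants are picked at random from a listing. This stands for enumerators, who may well remain unaware. A reader might infer that concealment fails for everyone in Cohorts 2 and 3; the document supports that only for partners and stakeholders, through the release of the list and local delivery.

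**Table 7 may be illustrative.** Sequence generation {16a} refers to it as a sample randomization. But it lists real sub-counties, its caption calls it the selected sample, and its count equals the abstract's. If it is illustrative, the text still needs correcting.

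**Biased arms are not established.** This also stands. The dedicated recruitment section gives one route for both arms, so the trial design wording opens a risk and does not prove a mechanism. Nor is that risk confined to two thirds of the trial: if followed, it reaches all three cohorts.

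**Existing provisions help.** {11b} says cohort effects will be handled in the difference-in-differences analyses, {21b} plans analyses at Cohort 1 endline and follow-up, and {20b} plans models for each cohort. These supply much of the sensitivity analysis needed.

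**Two stronger readings fail.** A reader might attach a loss of power by assuming some leakage of the effect into later cohorts. The document gives no leakage rate and does not say that sub-counties host several cohorts. Nor is 80% the starting point on the printed inputs: with two-sided alpha 0.0125, 2 × (2.4977 + 0.8416)² × 0.45 × 0.55 ÷ 0.10² × 2.3 ≈ 1,270, or 1,411 per arm after 10% attrition, well below 1,872. A reader might also infer that {6b} and {13} conflict on wait-list delivery. They agree that it follows the follow-up assessment; overlap with later cohorts' controls arises only if sub-counties are shared.

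**Conclusion.** The concealment and blinding statements, Table 6 and Table 7 cannot all be right. If the 48 sub-counties were allocated once, concealment from implementing partners and sub-county stakeholders holds for Cohort 1 only, and about two thirds of the dyads (2,496 of 3,744, assuming equal cohorts) are recruited without it. This rests on the version date applying to Table 7 and on no fresh allocation being made for later cohorts. Separately, the protocol gives two incompatible sources for the intervention arm; following the trial design wording would select the arms differently in every cohort, Cohort 1 included. Neither point shows that bias has occurred, and the document offers no basis for sizing it. Both should be corrected, because they bear on the main protection of an open-label trial with reported outcomes.

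**What to change.** 1. Reconcile Table 6 with Table 7 and the abstract. If there was one allocation, limit the claims in {16b} and {17a} to Cohort 1 for partners and stakeholders, and say separately what enumerators know. If fresh allocations are made, correct Table 7 and the abstract.
2. Replace the trial design sentence, and align the introduction and {13}, with one rule for both arms: the evaluation team randomly selects participants from its own village listing, without partner input on individual fathers and before the programme selects fathers in that village. Apply it to every cohort not yet enrolled, and report how earlier cohorts were sampled. Partner outreach to communities in stage 1 of {10} can remain.
3. Prespecify a treatment-by-cohort term and a Cohort-1-only sensitivity analysis, building on {11b}, {21b} and {20b}. The Cohort 1 analysis addresses concealment; it addresses sampling only if Cohort 1 was drawn from the listing. If sub-counties host more than one cohort, add an analysis excluding villages with earlier programme or wait-list delivery.

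The cost is a weaker concealment claim, wider intervals in the sensitivity analyses, and some coordination in the field so that sampling precedes programme selection of fathers.

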### Implementation {16c}

Study randomization and outcome assessments are done by an evaluation team, while intervention implementation is done by an implementation team of partners, who are blinded to the outcome assessments. After randomization, a list of the sub-counties will be shared with the field implementation team for execution.

## Assignment of interventions: Blinding

### Who will be blinded {17a}

Sub-county stakeholders, trial participants, enumerators, and the implementing partners will be blinded to allocation until after recruitment and baseline measures are complete.

### Procedure for unblinding if needed {17b}

The study design is openly labeled, and so, unblinding of this behavior change intervention will not be possible.

## Data collection and management

### Plans for assessment and collection of outcomes {18a}

Data collection for this phased rollout cluster randomized controlled trial will take place at three points over the course of three cohorts: baseline, endline, and follow-up. Data collection will occur via face-to-face interviews by trained RAs roughly one month before the intervention begins (endline), one month after the intervention ends (baseline), and eight months after endline (follow-up). A mix of male and female RAs (six in each region, 36 in total) will be recruited along the following characteristics and skills: a minimum of a university degree, roughly ages 20–35 years (to foster rapport with the study participants), experience in survey enumeration, and native speakers of the regional languages. All selected RAs will undergo a three-day training on questionnaire administration, consent process and procedure, research ethics, and tracing of respondents. The training will utilize both roleplays, lectures, and PowerPoint presentations. The RAs will also be given an opportunity to try out the data collection tools in the form of roleplays and pre-testing exercises to further build the speed to administer and understand the process of questionnaire administration. Well-performing RAs will be appointed as Field Supervisors (FS) and those who fall below the pass mark of the training test will be discontinued. Six data collection teams will be formed, one for each region. Each data collection team will comprise seven people including one FS, five RAs, and the co-I or other trained research team lead.

Two questionnaires have been developed—one for the fathers and one for the mothers. Both questionnaires have been translated and back-translated from English into six of the local languages spoken by the participants in each region: Ateso, Luganda, Langi, Lusoga, Runyakitara, Runyoro–Rutooro for the respective region. The research team will work with publishers of local newspapers and presenters of radio programs in the respective regions to ensure that the terms used in the surveys reflect the latest context, terms, and vernacular of the local dialects. All translated scripts will be harmonized in a conference of both translators and back translators moderated by the co-I. Additional translations and corrections of the item wording may occur during field training with the RAs before and after piloting with participants to ensure that the meanings of the items in English match the meaning of the local languages, thus helping to ensure more valid responses from the respondents.

Interviews with fathers will last approximately 70 min and interviews with mothers will last approximately 50 min. As much as possible, survey interviews will take place at the respondent’s home, or another private location where the conversation will not be overheard. Survey questionnaires will be programmed for Computer-Assisted Personal Interviews (CAPI) using XML file format in Kobo ToolBox software. Data will be captured through the KoboCollect app (v2024.2.4), an open-source Android application that runs on both mobile devices and computers and allows data export to the Windows operating system [53].All collected data will be stored in a password-protected, web-based database hosted on the KoboToolBox server. Each tablet used for data collection will be password protected to ensure data security. Data capture forms will be designed with inbuilt skips and validation criteria to reduce the chance of inconsistent or incorrect entries and also to enforce that all questions are responded to (with options of ‘don’t know/don’t remember’ and ‘refused’ possible in each question). Data will be checked for completeness and logical consistency before uploading from the mobile devices to the secure Kobo ToolBox server. Any query flagged for errors related to illogical or inconsistent entries will be shared with the responsible RA, and the co-I or field supervisor will consult with and possibly retrain the RA to address the issue, and re-contact the respondent as needed.

